### Participants and Procedure

The study population consists of patients aged 18 years or older with a primary alcohol problem, who are currently following TAU at Tactus Addiction Treatment Institute in the Netherlands. One general inclusion criterion is accessibility and ability to use the Internet, since patients will need to access CBM-training online. Two exclusion criteria apply for the TAU: (1) serious psychiatric illness with a risk to decompensate while decreasing alcohol consumption; and (2) the possibility of severe physical illness as a consequence of decreased alcohol consumption. There are no additional criteria for participation in this study.

Patients for the training are recruited by therapists at Tactus Addiction Treatment Institute. After the regular intake procedure, including baseline questionnaires, the TAU starts. Before the patient reaches the goal-setting assignment, the therapist will inform the patient about the CBM training and provide the patient with further information about the study. If the patient wants to participate, an informed consent form will be provided to patients by the therapist. After signing the form, the patient receives login credentials for the CBM training from the researcher.

After finishing registration, the patient is randomly assigned to the Alcohol Avoidance Training or to the placebo training, and receives an email with a link to the CBM training website. After logging in, the patient receives instructions about the training. At the start of each session, the patient is asked to complete the additional questionnaires for the purpose of this study, consisting of self-reported weekly alcohol consumption and desire for drinking. Each of the eight training session takes about 10-15 min. The first training session is preceded by an (online) preassessment and the final training session is followed by an (online) postassessment. Three and six months after the postassessment, each patient will receive online follow-up questionnaires. In case of nonresponse, the patient will be reminded by email or phone to complete the questionnaire.

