### Aims and Hypotheses

The aim of the current study is to investigate the effectiveness of online CBM Alcohol Avoidance Training as an adjunct to TAU in an outpatient treatment setting. Patients receive eight sessions of either the active or placebo version of the CBM Alcohol Avoidance Training during their TAU. The primary goal is to test the effects of this adjunct CBM on alcohol use immediately after finishing the intervention and three and six months later, by looking at the changes in the level of alcohol consumption over a week. The primary outcome measure is the percentage of the patients reaching the low-risk drinking level, defined as <22 standard units/week for men and <15 for women [29]. It is expected that more patients in the experimental condition will reach low-risk drinking level. Furthermore, it is hypothesized that the CBM intervention decreases or reverses the approach bias, and these changes are expected to mediate the effects on alcohol use [23]. An improvement in health status and a decrease in depression, anxiety and stress for patients in the training condition, compared to the placebo condition, are expected as secondary outcomes. To investigate who benefits most from the training, possible moderators will be examined. Automatic impulses may be controlled by cognitive capacity available to inhibit these impulses. Refusal self-efficacy is considered such a cognitive resource. Following this assumption, CBM interventions can yield benefits, especially for those with a relatively weak cognitive control over their impulses to drink [12,30-32]. In line with the predictions from dual process models and prior CBM trials [12], it is expected that for patients with a low baseline self-efficacy, the additional effect of the Alcohol Avoidance Training will be stronger. Similarly, time-varying self-efficacy is expected to partially mediate the CBM effect as repeated experiences of successful coping due to stronger avoidance responses will enhance refusal self-efficacy. Patients’ adherence and perceptions of treatment acceptability, and credibility will also be examined.

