## Methods

### Trial Design

This study is a double-blind randomized placebo-controlled trial in a real-world setting. Patients receive TAU, consisting of outpatient personalized care

All patients with a primary alcohol problem enrolled for TAU are invited by their therapist to participate in the Alcohol Avoidance Training. After giving informed consent, patients are randomly assigned to one of the two training conditions: CBM Alcohol Avoidance Training or CBM placebo training. Patients begin the training simultaneously with the start of the behavioral change part of their treatment. Patients are recommended to follow a 15-minute CBM session twice a week for a period of five weeks. The CBM training includes eight sessions, preceded and followed by an assessment session, the preassessment and postassessment, respectively. Patients will be rewarded with a € 20 voucher if they complete all ten sessions. Three and six months after the TAU there will be follow-up assessments. Figure 1 shows the participant flow chart of the study.

The study has been approved by the Ethics Committee of Amsterdam Academic Medical Centre in January 2015 (reference number 2014_154#C20141463) and has been registered at the Netherlands Trial Register (NTR5087).

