### Statistical Analyses

Analyses will be conducted in agreement with intention-to-treat principle. Missing data points will be handled using multiple imputation [53]. One-way ANOVAs and χ²-tests will be performed to see if there are any significant differences at baseline between the two CBM training conditions (Avoid Alcohol vs placebo) for any of the demographic variables or outcome measures. Nonsignificant differences will indicate successful randomization. To determine the primary outcome, a logistic regression analysis will be used to test the differences in the proportion of patients reaching the low-risk drinking criterion between the CBM Alcohol Avoidance Training and CBM placebo condition, both at posttest and at follow-up. If necessary, baseline confounders will be controlled for, and significant interaction effects will be further investigated using post hoc *t*-tests (independent samples *t*-test and paired samples *t*-test). Effect sizes on clinically relevant outcomes at postintervention and follow-up will be calculated by Cohen’s d using the means and pooled standard deviations of the measurements of the conditions. Effect sizes of .56-1.2 are considered large, .33-.55 are considered moderate, and less than .33 are considered small [54]. Repeated measures ANOVAs will be conducted to test for differences between the CBM Alcohol Avoidance Training and the CBM placebo condition on the secondary outcomes general health condition, depression, anxiety and stress. Mediation analyses will be conducted by applying the analytic procedure according to Preacher and Hayes [55] and Hayes [56] to examine whether a change in approach bias is mediating the Alcohol Avoidance Training effects on our primary outcome measure. Logistic regression analyses will be used to assess whether patient characteristics moderate the effect of the Alcohol Avoidance Training on our primary outcome measure. The procedure proposed by Baron and Kenny [57] will be adopted. Descriptive statistics will be used to investigate to what extent patients adhered to the Alcohol Avoidance Training (in terms of timing, frequency, and duration of sessions) and to what extent patients found the Alcohol Avoidance Training both acceptable and credible (testing adherence, acceptability, credibility).

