## Discussion

This study protocol design describes a double-blind randomized controlled trial to assess the added value of an online Alcohol Avoidance Training as adjunct to TAU for outpatient alcohol patients. Previous studies involving alcohol dependent patients in inpatient addiction treatment have shown promising results for Alcohol Avoidance Training in addition to TAU [21,23]. The present study wants to test whether the positive added effects found in a more controlled, clinical setting, with training on local desktop computers, are replicated when the training is administered in a less controlled, ambulatory setting with online delivery.

The online delivery of CBM training enables patients to conduct the sessions at a preferred location, which may entail some threats to treatment fidelity. The preferred environment might bring distractions like ambient sounds or the interaction with other people present, which could influence the concentration level and responsiveness to the training [57]. Therefore, patients will be instructed to avoid distractions and that concentration, accuracy and speed during the sessions is required. Another aspect to take into consideration is that online interventions typically have a high dropout rate [58]. Therefore, treatment adherence is encouraged by: (1) emails from the research assistant to the therapists to enable them to monitor the progress of their patients when, for example, the patient has not finished a training session for some time; (2) emails or oral messages from the therapist to the patient to reinforce motivation; (3) emails to invite, remind and praise patients regularly. These messages are generated automatically by the training program whenever a patient can start a new training session, or when patients do not start with a new training session after the designated time; (4) a gift voucher of €20 from an online shop (Bol.com) when upon completion of all 10 study sessions (8 training sessions, and pre- and postassessment).

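### The 3- and 6-month follow-up has two different starting points, and one of them is undefined for patients who stop the training early

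*Protocol article*

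**What the plan says.** All statements are in the protocol article.

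- **Trial Design:** "Three and six months after the TAU there will be follow-up assessments".
- **Participants and Procedure:** "Three and six months after the postassessment, each patient will receive online follow-up questionnaires". The same paragraph fixes when the postassessment happens: "the final training session is followed by an (online) postassessment". Nonresponders are reminded by email or phone.
- **Aims and Hypotheses:** effects on alcohol use are to be tested "immediately after finishing the intervention and three and six months later". This fits the postassessment clock better than the TAU clock.
- **Table 2:** Postassessment and Posttest TAU are separate columns. Weekly alcohol consumption, the basis of the primary outcome, is ticked in both, as well as at baseline, preassessment, training and follow-up.
- **Statistical Analyses:** the primary logistic regression is run at a posttest and at follow-up, with neither tied to a column of Table 2. "Analyses will be conducted in agreement with intention-to-treat principle", and missing values are to be multiply imputed.
- **Training schedule (Trial Design):** "Patients are recommended to follow a 15-minute CBM session twice a week for a period of five weeks". The pace is a recommendation only.
- **Discussion:** the authors expect that "online interventions typically have a high dropout rate", without giving a figure for this trial.

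**The concern.** The article gives two rules for when the primary outcome is measured at follow-up, and they cannot both be followed. It also leaves open which of two end-of-treatment measurements is the posttest in the primary analysis.

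The second difficulty lies in the postassessment rule itself. If the postassessment comes after the final session, a patient who stops at, say, session 3 has no postassessment date, and so no date three or six months after it. If the schedule is run that way, whether an outcome is requested depends on adherence. Adherence is observed after randomisation and plausibly relates to drinking. If it also differs between active and placebo training, the comparison could be biased.

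**Working it through.** **1. The two clocks side by side.**

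| Section | Clock starts at | Exists for a patient who stops CBM early? |
|---|---|---|
| Trial Design | TAU | Yes, if TAU is completed; no date is given for someone who also leaves TAU |
| Participants and Procedure | CBM postassessment | Not as written: it follows the final session |
| Aims and Hypotheses | Finishing the intervention | Not as written |

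**2. How far apart the clocks are for patients on schedule.** Inputs from the article: ten sessions (eight training, one pre, one post) at two a week take 10/2 = 5 weeks. "Patients begin the training simultaneously with the start of the behavioral change part of their treatment". Brief TAU lasts 5 weeks and consists of that part; intensive TAU lasts about three months. Table 1 puts sessions 1-5 in part 1 and 6-10 in part 2.

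- Brief TAU: gap = 5 − 5 = 0 weeks.
- Intensive TAU of L weeks with part 2 starting at fraction f: gap = L − (fL + 5). L = 12 or 13 and f = 0.4 to 0.6 are assumptions; equal session counts in Table 1 suggest f near 0.5.

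| L (weeks) | f = 0.4 | f = 0.5 | f = 0.6 |
|---|---|---|---|
| 12 | 2.2 | 1.0 | −0.2 |
| 13 | 2.8 | 1.5 | 0.2 |

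So training ends between about 3 weeks before TAU and the same time as TAU.

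**3. Patients off schedule.** Because the five weeks are only recommended, a patient who pauses moves the postassessment by the length of the pause, and a patient who stops never reaches it. The article sets no upper limit.

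**4. The planned sample size.** Inputs from Sample Size Calculation: 68% versus 81%, one-tailed 5%, power 0.80, Fisher's exact test. Exact power is the sum, over all pairs of binomial counts, of their joint probability wherever the one-sided Fisher p-value is at most 0.05. At 151 per arm it is 0.7999; at 152 it is 0.8030. The stated 152 reproduces, and no follow-up date enters the calculation.

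**5. Illustration of lost outcomes.** The article cites full completion of 81% and 85% in CBM studies of depression and anxiety. Applied here as an assumption:

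- 85%: 152 × 0.85 = 129 per arm (23 lost), power 0.735.
- 81%: 152 × 0.81 = 123 per arm (29 lost), power 0.714.
- If completion were 70% (106 per arm), power 0.652; if 50% (76 per arm), 0.509.

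These values hold only if every non-completer has no outcome and is left out of the analysis. The plan is to impute, so they are not a forecast.

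**The case against.** A reader might infer that non-completers have no outcome at all and that the intention-to-treat analysis therefore fails. The article does not support that.

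- Follow-up is promised to each patient, with reminders. Nowhere is it said that someone who stops training is refused the postassessment or follow-up; that is inferred from the order of events.
- The TAU clock and the Posttest TAU column give measurement points that do not depend on finishing CBM.
- Randomised patients stay in the analysis through multiple imputation. Weekly consumption is also asked at the start of every training session, so partial completers supply data that can inform the imputation.

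Three further points deserve weight. Timing follow-up from the end of treatment is a legitimate choice and matches the stated aim, so variable time since randomisation is not in itself an error. On schedule the clocks nearly coincide. And this is a condensed article: a fallback date and visit windows are often left to the full protocol, and the flow chart, which may show the timing, is not visible here.

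These arguments limit the consequence but leave the contradiction. Two incompatible rules are stated, and one has no date for a foreseeable group of patients. The promise to each patient cannot be carried out for that group under the postassessment clock. Imputation does not recover answers never requested, and it may be biased if missingness depends on unobserved drinking.

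**Conclusion.** The point holds as an inconsistency in the timing of the primary outcome. The follow-up anchor differs between sections, the posttest used in the primary test is not identified, and the postassessment anchor is undefined for patients who do not reach the last session. The resulting risk is outcome collection that depends on adherence, with possible bias that imputation may not remove.

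For patients on schedule the size is small: about 0 to 3 weeks, resting on the assumed length and split of intensive TAU. For those who pause or stop, it is unbounded. How many that will be cannot be said, since the article gives no dropout figure for this trial. The sample size of 152 per arm stands. The power range of 71-74% shows only what complete-case loss would cost at an assumed 81-85% completion; it should not be read as the power of this trial.

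**What to change.** 1. Reconcile Aims and Hypotheses, Trial Design, and Participants and Procedure to one anchor that exists for every randomised patient, whether or not CBM or TAU is completed. One option is the planned end-of-training date counted from randomisation or training start. It could apply to everyone, or at least serve as the fallback for patients who stop early. The second variant keeps the stated aim of measuring after the intervention for those who finish.
2. Send the weekly-consumption TLFB to all randomised patients at that date and three and six months later, whatever they completed.
3. In Statistical Analyses, tie posttest to one named column of Table 2.
4. For patients already followed, analyse by actual assessment dates with a stated visit window.

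The cost is a wording correction and a change to when questionnaires are sent; the article does not say how follow-up questionnaires are triggered, so the effort for the latter is unknown. There are two downsides. For slow patients a fixed date may fall before training is finished, and a change during recruitment mixes two schedules, which is why step 4 is needed. Recruitment was still open when the article was written, so later outcomes could still be collected on a common rule.

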### Interventions

#### Treatment as Usual

TAU in this outpatient treatment setting is based on principles of CBT [33] and motivational interviewing [34]. The specific form of the TAU is tailored to the individual needs of the patient, in terms of treatment modality (Web-based or face-to-face) and intensity (brief 5-week version or intensive 3-month version). Study participants, therefore, receive an individualized version of treatment, as is common in regular real-world treatment settings. However, the basic ingredients for all versions are identical: daily registration, the analysis of the functions of the patients’ drinking behavior, behavioral change components, and motivational interviewing. Table 1 provides an overview of the main treatment ingredients. Sessions in face-to-face and Web-based treatment are identical. The only difference is that the contact with the therapist is synchronous in face-to-face treatment, and asynchronous via the Internet in the Web-based treatment [35]. The intensive version of the treatment takes approximately three months with (online or face-to-face) sessions once or twice a week and daily self-reporting of alcohol intake during the whole program. This treatment consists of two parts: a first part focusing on the analysis of the patients’ drinking habits, and a second part starting with the goal setting assignment, followed by sessions geared towards helping the patient reach the set goals and desired behavioral change. The brief 5-week version of the treatment focuses solely on behavioral change (part 2) and is intended for patients who already gained insight into their drinking habits when starting with treatment.

As we are interested in the effectiveness of online CBM Alcohol Avoidance Training as an adjunct to TAU, we do not differentiate between these four treatment “subgroups.” Due to the randomization, the experimental and control group are expected to be balanced concerning treatment modality and intensity.

Therapists have either a bachelor’s degree in social work or a master’s degree in psychology, and received a 2-day training on the treatment protocol of the TAU. Therapists can obtain expert advice from a multidisciplinary team consisting of treatment staff, an addiction physician specialized in addiction, a psychologist, and a supervisor. This multidisciplinary team also provides quality assurance through monitoring of client files and discussing treatment fidelity with counselors during weekly review of clients.

#### CBM Training

The intervention used in this study is the Alcohol Avoidance Training [21,23], based on the Approach-Avoidance Task (AAT) [36]. In this training, pictures of alcoholic beverages or soft drinks are presented, which are tilted 3 degrees to the left or right. Patients are instructed to respond to the tilted format of the picture, and not to the picture itself. This so-called irrelevant-feature version of the training (ie, responding to the format of the picture and not the subject of the picture itself) is used [21,23] because it is more indirect [37], and therefore blinds condition allocation (training vs placebo). Another advantage is that it is possible to change from measurement to training without changing the content of the picture set [38]. Striking the selected “u” key causes an avoidance movement of pictures in one format (eg, tilted left), while striking the selected “n” key causes an approach movement of pictures in the other format. The approach movement increases the size of the picture, and the avoidance movement decreases the size. This zooming effect generates a sensation of approach or avoidance, respectively. The combination of the format of the picture and the response (left=avoid and right=approach, vs left=avoid and right=pull) is counterbalanced across patients.

**Figure 1 figure1:**
[figure not shown]
Participants flow chart. TAU: treatment as usual; CBM: Cognitive Bias Modification.

**Table 1 table1:** Overview of the main treatment ingredients in intensive and brief treatments.

Session^a^	Content	Intensive (face-to-face/Web)	Brief (face-to-face/Web)
1	Baseline assessment	✓	✓
2	Advantages and disadvantages	✓	
3	Daily drinking diary	✓	
4	Description of drinking moments	✓	
5	Analysing drinking situations	✓	
6	Goal setting	✓	✓
7	Helpful thoughts	✓	✓
8	Helpful behavior	✓	✓
9	Decision moments	✓	✓
10	Action plan	✓	✓

^a^Part 1 is comprised of sessions 1-5 and part 2 is comprised of sessions 6-10.

The complete training program consists of eight sessions. Each session starts with a practice block of 12 trials with gray squared pictures followed by 160 trials divided into 4 blocks. The use of blocks was adopted to make the task less monotonous and to provide a short break. Two sets (A and B) of 40 stimuli each are used of which 20 are for alcoholic beverages and 20 for soft drinks [39]. Patients randomly received either set A or set B for assessment and the other set for training to be able to test generalization to untrained stimuli. In the training condition, all 40 stimuli are repeated 4 times (alcoholic beverages in avoid format, soft drinks in approach format) to train patients to avoid alcohol by exposing them only to alcohol/push and soft drink/pull trials. In the placebo condition, all 40 stimuli are presented 4 times: 2 formats (tilted to the left or right) x 2 repetitions. Alcoholic beverages and soft drink pictures are presented equally often in both formats. Figure 2 shows an example of the Alcohol Avoidance Training. Stimuli stay on the screen for a maximum of 3000 ms. In the case of no response, the trial is restarted after repeating the instructions. Each trial starts with a fixation cross to keep patients’ attention focused.

